### Insecticide content (Dalamba, village A)

Insecticide content is the amount of active ingredient per gram of netting as determined by chemical assay. The net pieces of 30 cm^2^, cut from intact nets will be used to determine insecticide content. A sample from position 1 of the net will be included in baseline assays, but not in subsequent assays. Net samples will be weighed to estimate their density (mass of net per unit area) and then the samples from the same net will be combined for chemical analysis. The results will estimate the total active ingredient content of permethrin on the LLIN and pyriproxyfen and permethrin on PPF-LLIN. The Liverpool School of Tropical Medicine will conduct the chemical assay using analytical methods (Collaborative International Pesticides Analytical Council) recommended by WHO for quality control will be used to determine the total content of the active ingredient (unpublished method).

### Net survivorship (Sanako, village B)

To measure survivorship, all nets distributed to study subjects will be recorded. At each time point study nets will be visited and the physical presence of the net recorded. Those hanging over a bed will be considered as being in use. If the net is still present in the household, the investigator will record whether the net is being used for its intended purpose. Nets that have never been used will be recorded but excluded from the main analysis. If the net is no longer in the house, the investigator will determine how it was lost. This will be categorised as follows: loss by giving away the net to others to use either voluntarily (given to friends and relatives or sold) or involuntarily (stolen), and loss due to destruction, discarding or using it for alternative purposes because it is perceived as ‘useless’ [14]. These data will allow an estimation of the ‘hanging rate’ of bednets and allow us to better understand the reasons for net attrition.

### Fabric integrity (Sanako, village B)

Fabric integrity will be assessed from the questionnaire by counting the number of holes, including tears in the netting and split seams, by their location on the net and their size. Holes will be classified using the proportionate Hole Index (pHI) [14] into the following categories: good (pHI range 0 to 64), acceptable (pHI 65 to 642) and torn (≥643).

### Environmental measurements

The indoor temperature and relative humidity will be recorded continuously in 6 randomly-selected houses in each village from 0 to 36 months after net distribution to establish the environmental conditions present in the study houses. Data loggers (Lascar EL-USB-2-LCD Data Logger 80°C 100%RH) will be positioned at 1 metre above the floor on the wall nearest the foot end of the bed. Measurements will be made once an hour and the data will be downloaded every month.

### Measurement of adverse events

We consider that any AE arising from either net are highly unlikely. Nonetheless to document the safety of the use of these tools in a community setting, as in the main AvecNet Trial [9], residents will be followed for possible side effects of the PPF-LLIN by surveillance of known asthmatic subjects during the first month post-distribution and pregnancy outcomes will be monitored from antenatal clinic records.

### Safety considerations

There are no apparent risks to the safety of individuals or communities in this study. Permethrin-treated long-lasting nets have been fully evaluated by the WHO Pesticide Evaluation Scheme and approved for vector control (www.who.int/whopes/en/), and the products will be used in compliance with their recommended use and guidelines. The WHO hazard classification of permethrin is Class II, moderately hazardous [16]. The WHO hazard classification for pyriproxyfen is: U, unlikely to present acute hazard in normal use [16]. Pyriproxyfen is applied to drinking water sources for vector control because of its high insecticidal activity and low mammalian toxicity [3]. A recent WHO document [17] illustrates the low toxicity of pyriproxyfen for mammals: ‘*pyriproxyfen was not toxic when administered dermally to rats for 21 days at doses of up to 1,000 mg/kg of body weight per day. Inhalation of pyriproxyfen for 4 hours per day for 28 days caused only minor effects in rats (initial salivation, sporadically reduced body weight gain, slightly increased serum lactate dehydrogenase activity) at 10,000 mg/m*^*3’*^.

### Handling of drop-outs/withdrawals

If an individual wants to terminate his/her participation, no further follow-up will be performed. Net owners who have withdrawn consent, or are no longer in the study for whatever reason, will be replaced by other net owners resident in the same compound when possible. If a village opts out of the study during the first year, replacement by a neighbouring village will be considered.

### Study endpoints

#### Primary: bio-efficacy

Bio-efficacy is measured as percentage adult female mortality 24 hours after exposure to netting and as the percentage of viable offspring (first or second stage larvae) relative to the control group.

### Secondary: fabric integrity

Fabric integrity will be as defined earlier using the pHI [14] grouped into the following categories: good (pHI range 0 to 64), acceptable (pHI 65 to 642) and torn (≥643).

### Tertiary: net survival

Comparisons will be made between functional LLIN survival [14] with both types of nets.

### Tertiary: chemical analysis

The content of permethrin and pyriproxyfen in netting samples will be expressed in both g/kg and mg/m^2^.

### Sample size rationale

#### Primary outcome

##### Bio-efficacy - measured in Dalamba, village A

WHO expects that LLIN netting will kill at least 80% of mosquitoes that land on it. In this trial, however, the effects of the PPF-LLIN netting are not just on killing mosquitoes, but also causing sterility and reducing the number of offspring produced by female mosquitoes. A 50% reduction in killing when exposed to LLINs nets is likely to impact malaria vector control, as is a 50% decrease in the proportion of gravid females laying eggs after exposure to PPF-LLINs. In order to detect 50% reduction in killing from 80% to 40% and a coefficient of variation between clusters of 0.25, a conservative estimation, one requires 6 compounds with 4 nets, each with 3 netting samples/net/time, in each cluster to demonstrate a statistically significant impact at the 5% level and with 80% power. These calculations are based on the formula of Hayes and Bennett for clustered data [18]. For the 7 time points, one needs to recruit forty two compounds to each study arm.

#### Secondary outcome

##### Fabric integrity - measured in Sanako, village B

Since LLIN and PPF-LLIN are manufactured with the same fibre, the same weave and are manufactured by the same company we would not expect to find a difference in fabric integrity between them. However, a control programme manager might consider replacing all the nets in an area if > 25% were of poor condition. To estimate 25% nets in poor condition with a precision of ±10%, with a design effect of 1.0 because of cluster sampling, at the 5% level of significance, assuming there are either 500 LLINs or PPF-LLINs, would require 64 nets in each arm at the last sampling time. To allow for a loss of 10% of nets per year and for operational uniformity it is simplest to maintain the study framework of 100 nets in each group to allow for loss to follow-up if net users move away or stop using their nets; in which case, we would sample four nets in twenty-five compounds in each study arm. In addition, direct comparisons will be made between both nets.

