**Methods:**

This is a cluster randomised controlled trial of net durability in Burkina Faso, with clustering at the level of the compound and includes entomological outcome measurements. Half the compounds in each village will be randomly allocated PPF-LLIN and half the LLIN. All sleeping places in a compound will be provided with one type of net. We will distribute the nets at the start of the first transmission season and follow net use at the start and end of each transmission season for 3 years. In one village, bio-efficacy and chemical content will be recorded immediately after net distribution and then at 6, 12, 18, 24, 30 and 36 months. In the other village net survivorship and fabric integrity will be recorded immediately after distribution, and then at 6, 12, 18, 24, 30 and 36 months. Routine measurements of indoor temperature and relative humidity will be made in both villages during the study. Residents will be followed for possible side effects of the PPF-LLIN by surveillance of known asthmatic subjects during the first month post-distribution and pregnancy outcomes will be monitored from antenatal clinic records.

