### Net survival

The analysis will include data on all nets recorded at each time interval. The number of nets in the sample, the proportion of the indicator and 95% confidence interval will be reported. The following indicators will be used and disaggregated by survey time (for example, 0 weeks, 6, 12, 18, 24, 30 or 36 months):Survivorship:Numerator: total number of nets in ‘good’ condition (pHI 0 to 64) plus ‘acceptable’ condition (pHI 65 to 642) hung over a bed × 100Denominator: total number of each net type distributed to surveyed households, excluding a portion (those that may be still in use by others) of the number lost by attrition

Attrition rate-1 for nets that have been destroyed or disposed of:Numerator: total number of each net product documented as lost due to wear and tear(‘torn’, pHI > 642) in surveyed households × 100Denominator: total number of each LLIN type distributed to surveyed households, excluding the number lost by attrition

Attrition rate-2 for nets not available for sleeping under:Numerator: total number of each net product reported as lost for reasons other than ‘torn’ (given away, stolen, sold or used in another location) in surveyed households × 100Denominator: total number of each net product distributed to surveyed householdsAttrition rate-3 for nets used for other purposes:Numerator: total number of each net product reported as being used for another purpose in surveyed households × 100Denominator: total number of each net product distributed to surveyed householdsFor each net product, the survivorship rate plus attrition rate-1, attrition rate-2 and attrition rate-3 will add up to 100%.Kaplan-Meier survival analysis will be used to assess survivorship of nets with the log rank test being used to ascertain whether there are statistically significant differences between the two types of netting.

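### Village B: the fabric-integrity precision makes no allowance for clustering by compound (design effect 1.0), and net survival is compared with an ordinary log-rank test although compounds are randomised

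*Protocol article*

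**What the plan says.** The abstract describes a cluster randomised trial "with clustering at the level of the compound" and adds: "All sleeping places in a compound will be provided with one type of net".

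Under Sample size rationale, Secondary outcome, the village B aim is: "To estimate 25% nets in poor condition with a precision of ±10" percentage points. The inputs are a calculation "with a design effect of 1.0 because of cluster sampling" and "at the 5% level of significance, assuming there are either 500 LLINs or PPF-LLINs". The result is that this "would require 64 nets in each arm at the last sampling time". The frame is then raised to 100 nets per arm, as four nets from each of 25 compounds: "To allow for a loss of 10% of nets per year" and for operational uniformity.

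Two other places bear on this. Study procedures and evaluations says that every available village B net is surveyed at each visit. Sample size rationale, Tertiary outcomes, gives the counts as 374 LLINs and 167 PPF-LLINs.

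For survival, the Data analytical plan under Net survival states: "Kaplan-Meier survival analysis will be used to assess survivorship of nets with the log rank test being used" to judge significance between net types. It mentions no compound term. The Fabric integrity part of the same plan does adjust its between-treatment models for compound.

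**The concern.** The design-effect sentence contradicts itself: it gives cluster sampling as the reason for a value that means no clustering. Nets in one compound share a household setting and its habits of use and washing, so their damage and loss are likely to be positively correlated. If they are, 64 nets carry less information than 64 independent nets and the stated precision is too optimistic.

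The survival comparison has the same weakness in a test. The ordinary log-rank variance counts each net as an independent unit, while the unit allocated to a net type is the compound. Any positive within-compound correlation makes that variance too small. A chance difference in durability between net types would then be declared significant more often than 5% of the time.

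**Working it through.** **Inputs from the protocol article.** Proportion p = 0.25, half-width d = 0.10, z = 1.96, N = 500 nets, design effect (DE) 1.0, loss 10% per year, m = 4 nets per compound, 25 compounds per arm, 374 and 167 nets actually distributed.

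**Assumed, because the article does not give them.** The ICC, the nets per compound when all nets are surveyed, and the between-compound frailty variance.

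**1. The stated figure.** n = DE·N·p(1−p) / [(d/z)²(N−1) + p(1−p)].
- DE 1.0: 63.1, rounded up to 64. This is the stated number.
- DE 1.1 already gives 70 and DE 1.5 gives 95. The 1.0 is therefore the value used, not a misprint for a larger one.

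**2. With clustering.** DE = 1 + (m − 1)·ICC. Nets left from 100 at 36 months: 100 × 0.9³ = 72.9. Half-width = 1.96·√[DE × 0.1875/72.9 × (500 − 72.9)/499] = 0.092·√DE.

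| ICC (assumed) | DE at m = 4 | Nets needed at 36 months | Half-width with 72.9 nets |
|---|---|---|---|
| 0.05 | 1.15 | 73 | 9.9 points |
| 0.10 | 1.30 | 82 | 10.5 points |
| 0.20 | 1.60 | 101 | 11.6 points |

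Setting the half-width to 0.10 gives a tolerable DE of (0.10/0.092)², about 1.18, or an ICC of about 0.18/3 = 0.06. The sample-size formula gives 72.9/63.1 = 1.16; it differs slightly because it applies DE after the finite-population correction.

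**3. If losses also shrink the compounds.** Random loss from four nets per compound leaves an effective m of about 3.2. DE is then about 1.11, 1.22 and 1.44, the need 70, 77 and 91 nets, and the half-width 9.7, 10.2 and 11.0 points.

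**4. If all nets are surveyed.** PPF-LLIN: 167 × 0.729 = 121.7. LLIN: 374 × 0.729 = 272.6. Without the finite-population correction, an independent sample needs 1.96² × 0.1875/0.01 = 72.0 nets. The tolerable DE is 121.7/72.0 = 1.7 for PPF-LLIN and 272.6/72.0 = 3.8 for LLIN. More nets per compound use up this margin: at 8 per compound and ICC 0.10, DE = 1 + 7 × 0.10 = 1.7.

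**5. Log-rank type I error.** Simulation with no true difference: 374 against 167 nets in whole compounds, shared frailty within compound, six-monthly visits, ordinary log-rank test at 5%, 3,000 to 4,000 runs per setting. The 27% failure is 1 − 0.9³, from the article's loss rate. The 50% is an assumption that leaves room for torn nets counting as failures. With no clustering, at 4 nets per compound and about 50% failure, the test rejects 5.0% of the time.

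| Nets per compound | Failure by 36 months | Frailty variance 0.25 | Frailty variance 0.5 |
|---|---|---|---|
| 4 | 27% | 6.9% | 9.4% |
| 6 | 27% | 9.2% | 12.4% |
| 4 | 50% | 8.6% | 12.6% |
| 6 | 50% | 11.6% | 17.6% |
| 8 | 50% | 13.2% | 19.7% |

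Repeat runs differ by one or two percentage points. The range is about 7% to 20%.

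**The case against.** The strongest reply is that little of practical weight is lost. It has four parts.

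- **The 100-net frame is not the survey.** All village B nets are to be examined, so the smaller arm keeps ±10 points up to a design effect of about 1.7. This stands. It makes the precision half mainly a correction of the stated basis. It does not help the log-rank test, whose error rises with nets per compound.
- **Clustering is recognised elsewhere.** The village A calculation uses a formula for clustered data, and the bio-efficacy and fabric-integrity models adjust for compound. This stands too. A reader might infer that village B disregards clustering throughout, but the article does not support that.
- **The sizes rest on assumed inputs.** No ICC or compound count for village B is given. In village A, 649 nets over at least 84 compounds average at most 7.7, so 8 per compound is a high value. The only stated loss rate gives 27% failure, where inflation is milder. This is why a range is reported. The direction holds for any positive correlation.
- **The SAP may supply the detail.** This fails for the test itself: the article names the log-rank test as the means of judging significance. It succeeds for confidence intervals. A reader might infer that the village B intervals will be too narrow, but the article states no method for them.

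**Conclusion.** Both statements are wrong as written and should be corrected.

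The 64 nets per arm contains no clustering allowance. Under ICCs of 0.05 to 0.20 at four nets per compound, the need is about 73 to 101, or 70 to 91 if losses thin the compounds. It would be tempting to say that ±10 points is not delivered. The figures do not support that in general: the 100-net frame meets it up to a design effect of about 1.18, and the full survey up to about 1.7 in the PPF-LLIN arm.

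The log-rank test is anticonservative under positive within-compound correlation, with type I error of about 7% to 20% under the assumptions above. The upper end needs large compounds, high failure and the larger frailty variance.

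What is affected is a secondary precision statement and a tertiary test. The primary bio-efficacy conclusion and the between-arm fabric-integrity model are untouched.

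**What to change.** 1. Restate the fabric-integrity precision with design effect 1 + (m − 1)·ICC. State the nets per compound and an ICC range, and base it on all nets surveyed in each arm after expected loss.
2. Replace the ordinary log-rank test with a method that respects compound randomisation. Options are a Cox or discrete-time model with compound frailty or compound-robust variance, or a permutation test that re-allocates whole compounds within the size strata. Kaplan-Meier curves can stay as description.
3. State how the confidence intervals for village B proportions allow for compound. This is a clarification only.

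The cost is a slightly less favourable stated precision and minor analysis work. No extra nets or visits are needed.

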#### Tertiary outcomes

##### Net survival - measured in Sanako, village B

For simplicity and to maximise precision of this measure, all nets will be sampled at 6-monthly time intervals: that is 374 of LLIN and 167 of PPF-LLIN. Direct comparisons of functional LLIN survival will be made between both net types using Kaplan-Meir analysis.

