### Fabric integrity

Three indicators will be calculated at each survey time: 1) the proportion of torn nets, 2) the proportion of nets with holes and 3) a hole index.

Proportion of nets in poor condition (with 95% confidence interval):Numerator: total number of each type of net where the nets are not long enough to be tucked under the mattress, or are torn or badly damaged, or have more than 5 holes (finger-width, approximate diameter 2 cm)Denominator: total number of each net type found and assessed in surveyed households

Proportion of nets with any holes (with 95% confidence interval):Numerator: fabric integrity will be defined using the pHI [14] grouped into the following categories: good (pHI range 0 to 64), acceptable (pHI 65 to 642) and torn (pHI ≥ 643)Denominator: total number of each net type found and assessed in surveyed households

The hole index would be calculated as:

Hole index = (0.5 to 1.9 cm^2^ × number of size-1 holes) +(2.0 to 9.9 cm^2^ × number of size-2 holes) + (10.0 to 24.9 cm^2^ × number of size-3 holes) + (≥25.0 cm^2^ × number. of size-4 holes)

The holes will be weighted according to the average area of each hole category. For the hole size categories described above, the weights would be 1, 23, 196 and 578, which corresponds with the areas estimated on the assumption that the hole sizes in each category are equal to the mid-points.

For each net type, the mean and standard deviation as well as the median and inter-quartile range of the hole index will be determined. Comparisons between treatments at different periods will be made using generalised linear models, adjusting for compound.

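### The 64 nets per arm for fabric integrity rest on a finite population of 500 nets of each type that the protocol contradicts; without that correction the same inputs need 73

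*Protocol article*

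**What the plan says.** The calculation is in the protocol article under Sample size rationale, Secondary outcome, Fabric integrity. The aim is "To estimate 25% nets in poor condition with a precision of ±10" per cent, "with a design effect of 1.0 because of cluster sampling", "at the 5% level of significance". The section then says: "assuming there are either 500 LLINs or PPF-LLINs, would require 64 nets in each arm at the last sampling time". To cover a 10% loss of nets per year it plans 100 nets per group, as four nets in each of 25 compounds, and adds that the two net types will be compared directly.

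Other sections bear on this:

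- Randomisation and blinding gives 541 nets for village B, both types together, and allocates net type by compound.
- Net survival, under Tertiary outcomes, splits the village B nets as "374 of LLIN and 167 of PPF-LLIN".
- Study procedures and evaluations has every available net in village B surveyed at each time point.
- The Secondary objective concerns the physical integrity of the two net types over 36 months.
- Data analytical plan, Fabric integrity, calls for 95% confidence intervals on the proportions and for generalised linear models comparing treatments, adjusted for compound.

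**The concern.** The clause "assuming there are either 500 LLINs or PPF-LLINs" is what brings the requirement down to 64. It raises two problems.

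- **The input is contradicted.** Fabric integrity is measured only in village B, and neither arm there has 500 nets.
- **The correction does not fit the inference.** A finite-population correction suits describing one closed stock from a part of it. Here the results are meant to characterise two products, guide a programme manager's decision on replacing nets, and compare the types. The nets in one village stand for a wider population of such nets.

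At stake is whether the stated precision at the last survey is backed by the stated number, and how much room the 100-net framework leaves for losses. The article also offers itself as a model for other durability studies, so the derivation may be copied.

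**Working it through.** **Inputs (Fabric integrity sample size section).** p = 0.25, d = 0.10, design effect 1.0, N = 500. The 5% level is taken as two-sided, z = 1.96; sidedness is not stated, but this value reproduces the plan's figure.

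**Step 1: reproduce 64.**

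- Uncorrected: n0 = z²p(1−p)/d² = 3.8416 × 0.1875 / 0.01 = 72.03, rounded up to 73.
- Corrected: n = n0 / (1 + (n0 − 1)/N) = 72.03 / (1 + 71.03/500) = 63.07, rounded up to 64.

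The plan's figure is reproduced. A one-sided z without the correction gives 50.7, so 51, and does not reproduce it.

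**Step 2: use the protocol's own net counts, keeping the correction.**

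| N | Source | Corrected n | Rounded up |
|---|---|---|---|
| 500 | assumed per type | 63.07 | 64 |
| 541 | village B, both types | 63.67 | 64 |
| 374 | village B, LLIN | 60.53 | 61 |
| 167 | village B, PPF-LLIN | 50.53 | 51 |

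Correcting N alone lowers the requirement. The increase to 73 comes only from dropping the correction.

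**Step 3: does the correction belong?** If it is carried through, the half-width is multiplied by √((N − n)/(N − 1)). When every net in the population is surveyed, n = N and the factor is zero, so there is no sampling error left to report. The analysis section nevertheless plans intervals and model-based comparisons, which treat the nets as a sample from something larger.

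**Step 4: precision without the correction.** Half-width = 1.96 × √(0.1875/n), design effect 1. Three years of 10% compounded loss leave 0.9³ = 0.729 of the nets.

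| Situation at month 36 | Nets | Half-width (points) |
|---|---|---|
| Exactly the stated requirement | 64 | ±10.6 |
| 100 issued, compounded loss | 72.9 | ±9.9 |
| 100 issued, linear loss (30%) | 70 | ±10.1 |
| All PPF-LLIN, 167 × 0.729 | 121.7 | ±7.7 |
| All LLIN, 374 × 0.729 | 272.6 | ±5.1 |

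**Step 5: reserve in the 100-net framework.** Ending with 64 nets requires 64/0.729 = 87.8, so 88 at issue. Meeting the uncorrected requirement needs 72.03/0.729 = 98.8 at issue, or 73/0.729 = 100.1 if the rounded figure is used. Against 64 the framework appears to have about 12 nets to spare. Against the uncorrected requirement it has about none.

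**The case against.** The strongest reply has four parts.

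- **The finite population is disclosed and 64 follows from it.** This stands: there is no arithmetic slip.
- **The false N does not cause a shortfall.** A reader might infer that 64 is too small because 500 nets per arm do not exist. The protocol's figures do not support that, since the true counts with the same correction give 61 and 51. Any N from about 496 to 566 also rounds to 64, so the 500 may be a rounded village total. That would explain the number, but the sentence applies it per arm.
- **Leaving out the correction is a judgement.** A replacement decision can be framed as a question about a bounded stock of nets, and the analysis section gives no interval formula, so it does not say that the correction would be applied there. This stands in part: Step 3 shows poor fit, not a formal contradiction. The objective about net types, the direct comparison and the planned models still favour omitting it.
- **No precision is lost in practice.** A reader might infer that the ±10 target fails or that the allowance for losses is gone. Neither follows. The plan does not issue 64 nets; 100 per group leave 72.9, which gives ±9.9, so the allowance is used for its purpose. Surveying every available net does better still. The ±10.6 applies only if exactly 64 nets remain.

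**Conclusion.** The point holds as a badly founded sample size figure, not as a failure of the design. The 64 depends on a population of 500 nets of each type, which the protocol contradicts with 374 and 167, and on a correction that does not suit inference about net types. Without it, the same inputs need 73.

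The practical effect is small. At design effect 1, the 100-net framework meets the target under compounded loss (±9.9) and misses it trivially under linear loss (±10.1), with almost no reserve either way. The full survey meets it comfortably in both arms.

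This rests on a two-sided 95% interval, the plan's 10% yearly loss, and a design effect of 1. The last is the most favourable case, because net type is allocated by compound. Purely as an illustration, an assumed intraclass correlation of 0.05 to 0.20 with four nets per compound gives a design effect of 1 + 3 × 0.05 = 1.15 to 1 + 3 × 0.20 = 1.6, and raises 72.03 to 83 to 116 nets. That is a separate matter, but it means the ±7.7 and ±5.1 should not be read as what the trial will deliver.

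**What to change.** In the Fabric integrity sample size section:

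1. Delete the assumption of 500 nets of each type.
2. Restate the requirement as 73 nets per arm at month 36, before any design effect.
3. Say whether fabric integrity uses the 100-net subsample or all available nets, and state the expected precision for the nets actually issued and surveyed. With all nets and 10% loss per year, this is about ±7.7 points for the 167 PPF-LLIN and ±5.1 points for the 374 LLIN.
4. Label these as best-case values at design effect 1 that widen with clustering by compound.

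The cost is restated text and figures only, with no extra nets, visits or analyses.
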